## Intervention

### Routine care for all participants

All participants will receive routine care designated for discharged patients at each study site, in which an information leaflet about the benefits of adhering to health behaviors and medication, and the time points for follow-up visits will be distributed to all patients. In addition to the baseline questionnaire (T0) completed before participants are discharged from hospitals, all participants will need to complete a set of electronic questionnaires on the *iCARE* patient app and answer questions by telephone at 1 (T1), 3 (T2), 6 (T3), 12 (T4), 24 (T5), and 36 (T6) months after they are discharged from hospitals. Participants’ responses to these questionnaires will be used to evaluate the study outcomes. Each participant will receive 100 RMB (equivalent to 14 USD) to reimburse any costs (time, internets services, etc.) associated with participation of the trial. All participants will receive a wrist watch which has functions of monitoring their heart rate and counting daily steps.

### Intervention group

Patients randomized to the intervention arm will receive individualized care delivered via the *iCARE*-1 plus routine care over a course of 36 months. After participants complete the baseline assessment, they will receive a personalized initial health report which describes their medical and nursing diagnosis, modifiable unhealthy behaviors and health factors, along with established goals and action plans for risk reduction. They can also access individualized interventions with visual formats (such as animation, video, cartoon, and picture) for facilitating their adherence to health behaviors and medications. The interventions of *iCARE*-1 were developed based on existing evidence-based health behavior change strategies, and the mediators and moderators identified in the CAM model [42]. Participants in this group can enter their health-related data into the *iCARE*-1 by manual entry. These include diet, number of cigarettes smoked, level of physical activity, lipid profile, fasting blood glucose, hemoglobin A1c, blood pressure, heart rate, and weight. Information on participants’ heart rates and daily steps can also be synchronized through a smart watch. All data will be uploaded to the cloud platform and the tele-monitoring system for analysis. Instant and individualized feedback and tailored recommendations will be automatically sent to the care-provider app based on the built-in algorithms for verification by cardiovascular nurses. Verified interventions will be automatically sent to participants on *iCARE*-1. The described study design will not change once recruitment begins. However, participants are informed of options on stopping receiving the interventions at any time, during the consent process.

### Control groups

*Control group 1* participants in control group 1 will receive routine care plus interventions via the *iCARE*-2 in which all interventions are delivered only via text format.

*Control Group 2* participants in control group 2 will receive routine care and be asked to install the *iCARE*-3 before they are discharged. The *iCARE*-3 allows us to collect patients’ baseline and follow-up information through the app therefore to minimize information bias in estimation of the intervention effect.

### Outcomes

#### Primary outcome

The primary outcome of this study is the occurrence of MACEs, a binary variable based on the occurrence of AMI/ACS/stable angina, coronary revascularization, stroke, hospitalized heart failure, or death attributable to any cardiovascular disease [3], during the study period. Methods to ascertain MACEs are described in the Additional file 2. Based on the criteria for MACEs, information on the primary outcome will be systematically obtained through follow-up interviews at 1, 3, 6, 12, 24, and 36 months, and confirmed by reviewing patients’ medical records. If a patient dies during follow-up, this information will be obtained directly from patient’s family or confirmed by physician. All investigators in this study will attend rigorous training on data collection and research protocol. Table 1 presents all outcome measures and the time points when they will be assessed.

**Table 1 Tab1:** Standard Protocol Items (SPIRIT): details on the scheduled activities related to patient enrollment, interventions, and study variables at different time points

	Study period							
	Enrollment	Allocation	Post allocation					Closeout
Time point	−T_1_	T_0_	T_1_	T_2_	T_3_	T_4_	T_5_	T_6_
*Enrollment*								
Eligibility screen	X							
Informed consent	X							
Allocation		X						
Interventions		X	X	X	X	X	X	X
Assessments								
Major cardiovascular events			X	X	X	X	X	X
*Health behaviors*								
Smoking status		X	X	X	X	X	X	X
Dietary intake		X	X	X	X	X	X	X
Physical activity		X	X	X	X	X	X	X
Medication adherence		X	X	X	X	X	X	X
*Anthropometry parameters*								
Weight		X	X	X	X	X	X	X
Body mass index		X	X	X	X	X	X	X
Waist circumference		X	X	X	X	X	X	X
*Biochemical parameters*								
Total cholesterol		X		X	X	X	X	X
Low-density lipoprotein cholesterol		X		X	X	X	X	X
High-density lipoprotein cholesterol		X		X	X	X	X	X
Fasting blood glucose		X		X	X	X	X	X
Hemoglobin A1c		X		X	X	X	X	X
Systolic blood pressure		X		X	X	X	X	X
Diastolic blood pressure		X		X	X	X	X	X
10-year Framingham risk scores of cardiovascular risks		X		X	X	X	X	X
All-cause mortality			X	X	X	X	X	X
All-cause readmission			X	X	X	X	X	X
Frequency of medical treatment due to CHD			X	X	X	X	X	X
Patients’ engagement in the intervention			X	X	X	X	X	X
*Mediators and moderators of behavior change*^a^								
Risk perception		X			X	X	X	X
Outcome expectation		X			X	X	X	X
Action planning		X			X	X	X	X
Coping planning		X			X	X	X	X
Behavioral enjoyment		X			X	X	X	X
Social support		X			X	X	X	X
Self-efficacy		X			X	X	X	X
Effectiveness perception		X			X	X	X	X
Intention		X			X	X	X	X
Motivation		X			X	X	X	X
Volition		X			X	X	X	X
Stages of behavior change^a^		X			X	X	X	X
Knowledge of CHD		X			X	X	X	X
Perceived importance of health behaviors		X			X	X	X	X

CHD, coronary heart disease. −T1: Start point for patient recruitment; T0: Baseline; T_1_: 1 month; T_2_: 3 months; T_3_: 6 months; T_4_: 12 months; T_5_: 24 months; T_6_: 36 months

^a^The stages of behavior change, mediators and moderators of behavior change will be assessed dynamically

#### Secondary outcomes

The secondary outcomes of the study are summarized in Table 2 (the definitions and detailed measuring methods of all secondary outcomes are listed in Additional file 2). A copy of questionnaires for the study was shown in Additional file 3. Main secondary outcomes include changes in health behaviors, medication adherence, and cardiovascular health score:Healthy diet: dietary intake will be assessed by a short food frequency questionnaire (FFQ) which was developed according to the Chinese Guidelines on Cardiovascular Disease Prevention and previous study [43, 44]. The FFQ includes the amount and frequency of intakes on grains, vegetables, fruits, fish, and meat (poultry) in the past month [44]. The dietary pattern is categorized into three levels (ideal healthy diet, intermediate healthy diet, and poor diet) based on the recommended dietary goals from the European Guidelines on Cardiovascular Disease Prevention [7] and Chinese Expert Consensus on CHD Secondary Prevention [43].Physical activity: participants’ physical activity will be assessed by the simplified Chinese Version of the International Physical Activity Questionnaire (IPAQ), which was reported with acceptable test–retest reliability with intraclass correlation coefficients at 0.57–0.73 among Chinese population [45]. The IPAQ evaluates the intensity, frequency, and time spent on leisurely activities and occupational tasks in the past week. The scores of IPAQ will be converted to metabolic equivalents of task (METs) for each activity level based on the criteria from European Guidelines on Cardiovascular Disease Prevention [7]. Low physical activity refers to less than 600 METs/min/week [46].Smoking: participants’ smoking status will be assessed by a 32-item smoking status questionnaire which was adopted from previous research [44]. This questionnaire evaluates the frequency of smoking, number (current and past) of cigarettes smoked in the past 30 days, age started smoking among participants. Participants will be categorized as current smoker, former smoker, and nonsmoker. In addition, participants’ level of nicotine dependence will also be assessed using the 6-item Chinese version of the Fagerström Test for Nicotine Dependence (FTND) which has been documented to be a useful instrument for evaluating nicotine dependence in Chinese adults [47, 48].Adherence to secondary preventive medications: Medication adherence will be measured by the self-reported 8-item Morisky Medication Adherence Scale (MMAS-8) based on participant’s prescribed medications [49, 50]. The validated Chinese version of the MMAS-8 (C-MMAS-8) has a good internal consistency (Cronbach’s α = 0.77) and test–retest reliability [51], with the total score ranging from 0 to 8, and the higher the score, the better the medication adherence. The C-MMAS-8 includes 7 items with yes (“1”) or no (“0”) responses and one item on a 5-point Likert scale (0.2 to 1). Participants’ prescribed medications will be uploaded to the *iCARE* patients’ app before patients are discharged. Therefore, for patients in the intervention group and control group 1, the medication adherence will be also calculated by the *iCARE* patients app.Cardiovascular health: the American Heart Association defines the ideal cardiovascular health as simultaneous presence of four ideal health behaviors and three ideal metabolic indicators [8]. The four ideal health behaviors include nonsmoking, body mass index (BMI) < 25 kg/m^2^, physical activity at targeted level, and dietary consumption being consistent with current recommended guidelines. The three ideal metabolic indicators are identified as clinical parameters for blood pressure < 120/80 mm Hg, total cholesterol < 5.17 mmol/L (200 mg/dL) and fasting glucose < 5.60 mmol/L (100 mg/dL). Each component of the cardiovascular health metrics will be dichotomized as 1 (ideal status) or 0 (intermediate or poor status), and the cumulative number of ideal cardiovascular health metrics will be calculated to reflect patients’ overall cardiovascular health, with a possible range from 0 to 7 points [45].

**Table 2 Tab2:** The secondary outcomes and related measurements assessed in the iCARE study

Secondary outcomes	Measurements or tools
*Health behaviors*	
Dietary intake	A Short Food Frequency Questionnaire (FFQ) which was developed for this study according to the Chinese Guidelines on Cardiovascular Disease Prevention [43, 44]
Physical activity	The Simplified Chinese Version of the International Physical Activity Questionnaire (IPAQ) [45]
Smoking status	A 32-item Smoking Status Questionnaire which was developed for this study according to smoking history questionnaire from Lv et al. [44]
Medication adherence	A validated 8-item Chinese version of Morisky Medication Adherence Scale (C-MMAS-8) ^a^ [50, 51]
Cardiovascular health	American Heart Association Cardiovascular Health Score [8]
Anthropometry parameters	A Baseline Assessment Questionnaire (A) which was developed for this study
Biochemical parameters	Collected through follow-up visits with a Follow-up Assessment Questionnaire which was developed for this study and confirmed by reviewing medical records
All-cause mortality	Collected through follow-up visits with a Follow-up Assessment Questionnaire which was developed for this study and confirmed by reviewing medical records
All-cause readmission	Collected through follow-up visits with a Follow-up Assessment Questionnaire which was developed for this study and confirmed by reviewing medical records
Frequency of medical treatment	Collected through follow-up visits with a Follow-up Assessment Questionnaire which was developed for this study and confirmed by reviewing medical records
Patients’ engagement in the intervention	Data derived from iCARE platform: (1) the number of screens patients visited, (2) the frequency in uploading data, and (3) the number of interventions they accessed while using the patient application
Cardiovascular risks	10-year Framingham risk scores of cardiovascular risks tool [59]
*Mediators and moderators*	
Risk perception	A 4-item Risk Perception on Cardiovascular Risks Scale which was adapted from Renner and Schwarzer [60]
Outcome expectation	Outcome Expectation of Healthy Diet Scale, Outcome Expectation of Regular Exercise Scale, and Outcome Expectation of Quitting Smoking were from Renner and Schwarzer [60]. Outcome Expectation of Medication Management Scale was developed for this study
Action planning	Action Planning of Healthy Diet Scale, Action Planning of Regular Exercise Scale, and Action Planning of Quitting Smoking Scale were from Renner and Schwarzer [60]. Action Planning of Medication Management Scale was developed for this study
Coping planning	Coping Planning of Healthy Diet Scale, Coping Planning of Regular Exercise Scale, and Coping Planning of Quitting Smoking were from Renner and Schwarzer [60]. Coping Planning of Medication Management Scale was developed for this study
Behavioral enjoyment	Enjoyment of physical activity will be assessed using the 8-item Physical Activity Enjoyment Scale [61]. Enjoyment of healthy eating, smoking cessation, and adherence to medication therapy will be assessed with the scales adapted from Physical Activity Enjoyment Scale [61]
Social support	A 12-item validated Chinese Multidimensional Scale of Perceived Social Support (MSPSS) [62]
Self-efficacy	Self-efficacy of Diet Scale, Self-efficacy of Exercise Scale, and Self-efficacy of Quitting Smoking were from Renner and Schwarzer [60]. Self-efficacy of Medication Management Scale was developed for this study
Effectiveness perception	A 5-item Visual Analogue Scale (ranging from 0 to 10) of effectiveness perception of changes in blood pressure, lipid level, blood glucose, weight, and vascular plaque, which was developed for this study
Intention	A Visual Analogue Scale (ranging from 0 to 10) of intention to change unhealthy diet, physical inactivity, smoking was from Renner and Schwarzer [60]. Intention to change medication nonadherence scale was developed for this study
Motivation	A 4-item Visual Analogue Scale (ranging from 0 to 10) of motivation to change unhealthy diet, physical inactivity, smoking, and medication nonadherence, which was developed for this study according to Visual Analog Scale for motivation to quit from Vitor de Souza Brangioni et al. [63]
Volition	A 4-item Visual Analogue Scale (ranging from 0 to 10) of volition to maintain healthy behaviors and medication adherence, which was developed for this study
Stages of behavior change	A 4-item Stages of Behavior Change Scale [64]
Knowledge of CHD	Coronary artery disease education questionnaire (CADE-QII) [65]
Perceived importance of health behaviors	A Visual Analogue Scale (ranging from 0 to 10) of patients’ perceived importance of health behaviors [66]

CHD: Coronary heart disease

### Sample size calculation and power analysis

Based on previous studies [3, 4, 52], we anticipated that the 3-year incidence rate for cardiovascular events is 10% for patient with CHD. We estimated that a total of 2256 participants (752 per group) would provide 80% power to detect a 40% relative reduction [53] in MACEs (the incidence of MACEs is 10% for the control group and 6% for the intervention group, hazard ratio is 0.6), with 2-sided testing and alpha set at 0.05, and following a Cox proportional hazards regression method. According to previous studies [34, 54] and based on our pilot study, we anticipated a maximum attrition rate of 20% among all enrolled patients. Therefore, a total sample size of 2820 participants (940 per group) are needed in the present study.

### Data analyses

For baseline characteristics, categorical variables will be described as frequencies and proportions; continuous variables will be described as means and standard deviations, or medians and interquartile ranges where appropriate. Differences in baseline characteristics between the control and intervention groups will be detected using ANOVA test (continuous variables) or χ^2^ test (categorical variables) where appropriate.

Comparison of between group differences on the primary outcome will be performed according to both the intention-to-treat and the per-protocol principles. Simple χ^2^ analyses will be used to evaluate the main effect of the intervention on the MACEs at the end of the intervention period. Cox proportional hazards regression (with time to first event) will be used to estimate hazard ratios (HRs) comparing MACEs among three groups, by considering study group as an independent variable adjusted for covariates that are used for stratification (i.e., study sites, smoking status). The HRs and 95% *CI* will be calculated. Significant differences will be reported at the alpha level of 0.05 (two-sided).

All analyses related to secondary outcomes of the study are exploratory. The results of the analysis will be used to clarify the interpretation of the results related to the primary analysis, which include: changes in the proportion of adherence to health behaviors and medication, changes in anthropometry and biochemical parameters, etc. The mixed models and multilevel logistic regression models will be used to assess the differences in secondary outcomes between groups. Meanwhile, we will also explore whether the effects of intervention on the primary and secondary outcomes are consistent or not across subgroups of interest. Sensitive analyses will also be conducted.

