### Randomization and blinding

In this proposed study, three versions of *iCARE* apps will be installed on participant’s smart phone based on their group assignment (Additional file 1). Study investigators will assist participants in each group to download, register and log into the designated *iCARE* app:*iCARE*-1: is fully functional with individualized interventions delivered via multiple visual displays such as comics, videos, pictures, and text to address all the factors in the CAM model plus routine care;*iCARE*-2: is fully functional but all interventions are delivered only via text which did not address all factors in the CAM model plus routine care;*iCARE*-3: has limited function which only allows patients for daily data entry.

After baseline data collection, participants will be randomized to one of the three groups: the intervention group (*iCARE*-1 plus routine care), the control group 1 (*iCARE*-2 plus routine care), or the control group 2 (*iCARE*-3 plus routine care), following stratified block randomization. The randomization will be computer-generated by a statistician who will not have any active involvement in the study. The block size will be set at 15 with the allocation ratio set at 1:1:1 to ensure balance among three study groups. Participants will be stratified by 4 wards and their smoking status. The randomization assignment will be generated randomly, numbered consecutively, and will be kept in a sealed, opaque envelope. Patient assignment will be revealed to study researchers only after participants completed their baseline visit. This proposed study is an open-labeled trial as participants are fully aware of their intervention allocation, and the group assignments were known to study investigators. However, researchers who perform data analysis, and clinical staff who conduct laboratory testing will be unaware of the group assignment.

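### MACE is compared both by intention-to-treat and per protocol with no rule for which decides efficacy, and a per-protocol set based on intervention use can be biased against control group 2

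*Protocol article*

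**What the plan says.** The Data analyses section commits to two analyses of the primary outcome: "Comparison of between group differences on the primary outcome will be performed according to both the intention-to-treat and the per-protocol principles". It names a chi-square test ("Simple χ^2^ analyses will be used to evaluate the main effect of the intervention on the MACEs at the end of the intervention period") and a Cox model for time to first event, and gives one two-sided significance level of 0.05. It calls only the secondary-outcome analyses exploratory. It ranks neither principle above the other.

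The arms differ in what can be stopped. Under Intervention group, the article says that "participants are informed of options on stopping receiving the interventions at any time", over a 36-month course. Control group 2 receives routine care and iCARE-3, which "has limited function which only allows patients for daily data entry" (Randomization and blinding). Control group 1 receives a text-only intervention, which can also be stopped.

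The Quality control section adds that patients found to have been contaminated are removed from the study. It does not say from which analysis set.

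Table 2 shows that use of the app is recorded: "Data derived from iCARE platform: (1) the number of screens patients visited, (2) the frequency in uploading data", together with the number of interventions accessed.

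**The concern.** This is a superiority question, and two analyses of the same endpoint are planned at the same level with no stated order. Intention-to-treat compares the groups as randomized. A per-protocol analysis compares subsets formed by what patients did afterwards.

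Against control group 2 this matters more than usual, because that arm has no intervention content to give up. A set defined by receipt of the assigned intervention would keep persistent users in iCARE-1 and nearly everyone in control group 2. Patients who keep up a self-management app for three years may well have lower cardiovascular risk whatever the app does. That is plausible, but the documents do not quantify it.

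At stake is a trial with a null intention-to-treat result and a significant per-protocol benefit, and no prior statement of which one stands.

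**Working it through.** **The plan's own figure.** Inputs from Sample size calculation and power analysis: "the incidence of MACEs is 10% for the control group and 6% for the intervention group, hazard ratio is 0.6". The test there is a two-sided Cox regression comparison at the 5% level, and power is 80%.
- Schoenfeld events for a 1:1 pairwise comparison: 4 × (1.960 + 0.842)² / (ln 0.6)² = 120.3.
- Per group: 120.3 / (0.10 + 0.06) = 752. Rounding up to 121 events first gives 757.
- Power at 752 per group: 80.0%.
- Attrition: 2256 / 0.8 = 2820.

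The stated 752 and 2820 reproduce, so 752 per arm and 10% risk are used below.

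**Assumptions not in the documents.** f is the fraction of iCARE-1 patients removed for stopping. R is the risk of those removed relative to those kept. There is no true effect, and at first nobody is removed from control group 2.

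**Formulae.**
- Risk among retained iCARE-1 patients: p = 0.10 / (1 − f + fR).
- Number retained: n = 752(1 − f).
- z = (0.10 − p) / √[0.10 × 0.90/752 + p(1 − p)/n].
- Two-sided rejection probability: Φ(z − 1.96) + Φ(−z − 1.96).

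**Worked case, f = 20%, R = 2.** p = 0.10/1.2 = 0.0833 and n = 601.6. The standard error is 0.0157, so z = 0.01667/0.0157 = 1.06, and the rejection probability is 18.6%.

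| f | R | Apparent RR | Two-sided rejection |
|---|---|---|---|
| 20–40% | 1 | 1.00 | 5.0% |
| 20% | 1.5 | 0.91 | 8.8% |
| 20% | 2 | 0.83 | 18.6% |
| 30% | 1.5 | 0.87 | 12.5% |
| 30% | 2 | 0.77 | 30.4% |
| 40% | 1.5 | 0.83 | 16.5% |
| 40% | 2 | 0.71 | 41.7% |

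A simulation of 40,000 trials with a pooled-variance test gave slightly lower rates: 18% at f = 20%, R = 2, and 39% at f = 40%, R = 2. Nearly all of these rejections favour iCARE-1. Intention-to-treat stayed at 5% two-sided throughout.

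**If either analysis may carry the claim.** Even without prognostic selection (f = 30%, R = 1), the simulated chance that at least one of the two analyses shows a false benefit was 3.5%, against 2.5% for intention-to-treat alone.

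**If control group 2 is filtered too.** With R = 2 in both arms, the apparent RR is (1 + fraction removed from control) / (1 + fraction removed from iCARE-1).

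| Removed from iCARE-1 | Removed from control group 2 | Apparent RR |
|---|---|---|
| 30% | 10% | 1.1/1.3 = 0.85 |
| 30% | 20% | 1.2/1.3 = 0.92 |
| 30% | 30% | 1.3/1.3 = 1.00 |
| 20% | 30% | 1.3/1.2 = 1.08 |

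**The case against.** A reader might infer that the plan removes poor users from iCARE-1, that control group 2 has no counterpart at all, and that the per-protocol result must therefore favour iCARE-1. The documents do not support any of these.

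- The article does not define the per-protocol set. Patients may stop the intervention, but nothing says that they then leave that set. A definition of this kind is commonly left to the full protocol or analysis plan, so its absence is no fault here.
- Control group 2 also installs an app, and every participant completes app questionnaires at six follow-ups. A rule based on installation, data entry or completed visits would remove patients there as well, and the bias could then shrink, vanish or reverse.
- iCARE-1 and iCARE-2 both deliver an intervention that can be stopped, so their comparison does not share this asymmetry.
- The removal of contaminated patients would probably fall mainly on the control arms, and the calculation does not model it.
- f and R are assumed, and at R = 1 there is no inflation in the per-protocol test. Starting from 752 per arm also ignores any overlap between stopping and the 20% attrition allowance.
- Intention-to-treat is planned, is named first, and is untouched by this mechanism. Showing a per-protocol result beside it is common practice.

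All of this stands as a limit on size and direction. It does not remove the core of the point. A rule that can be applied in every arm still selects after randomization, and entering data is a different behaviour from engaging with tailored content, so equal selection is not assured. Nor does naming intention-to-treat first make it the deciding analysis.

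**Conclusion.** The point holds in a limited form. MACE is to be compared under two principles at one significance level, and the plan does not say which decides efficacy. One of the two selects on behaviour after randomization. If that selection depends on receiving the intervention, the contrast of iCARE-1 with control group 2 can show a benefit where none exists. With the assumed 20% to 40% stopping and stoppers at 1 to 2 times the risk of users, the apparent RR is 1.00 to 0.71 and the false-positive rate 5% to about 42%. These figures show what could happen under one kind of rule and do not predict what this trial will find.

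The elimination of contaminated patients is a further exclusion after randomization. Nothing suggests that it would offset the first, and applied to the intention-to-treat set it would weaken the one comparison that is otherwise protected.

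**What to change.** State in the analysis plan that intention-to-treat alone decides the MACE conclusion, that all randomized patients stay in that set whether or not contamination is reported, and that a per-protocol result cannot support an efficacy claim.

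If the effect of actual use is wanted, replace the per-protocol contrast of iCARE-1 with control group 2 by a complier-average causal effect. Use randomization as the instrument, and define use by a low threshold on the platform engagement data, fixed before unblinding. Its null hypothesis is that of intention-to-treat, so it keeps the error rate.

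The cost is wording and one extra model. The article says that analysis had not begun at submission. Intervals will be wider. The method also assumes that assignment has no effect on patients below the threshold. That is only approximate here, because iCARE-1 patients receive an initial health report with goals and action plans after baseline, however little they use the app later. A low threshold limits the problem. What remains affects the size of the estimate and leaves its null test valid.

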### Recruitment, screening, and baseline visits

To identify eligible patients, a targeted review of patients’ medical record based on the inclusion and exclusive criteria will be carried out, with referrals from nurses or clinicians within the study sites. Identified patients with CHD will participate in a formal screening session and have a baseline visit in the hospital. During the formal screening session, we will ask patients to complete an initial screening assessment which includes age, educational background, vision, hearing, diagnosis, heart function grade, etc. Patients who meet the study criteria will be asked to sign a written informed consent before attending the baseline visit. Participants’ baseline data will be collected via the *iCARE* care-provider app and patient app within one week of enrollment, which includes patients’ general characteristics, health behaviors (daily diet, physical activities, smoking status) and medication adherence in the past 30 days before admission, as well as their blood pressure, blood glucose, blood lipid levels during hospitalization.

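### The Cox model behind the sample size adjusts only for study site and smoking, leaving a modest gain in power from age, index diagnosis and heart function grade unused

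*Protocol article*

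**What the plan says.** Under Data analyses, the effect on MACEs is assessed in two ways: a simple chi-square test at the end of the intervention period, and a Cox model for time to first event "by considering study group as an independent variable adjusted for covariates that are used for stratification (i.e., study sites, smoking status". Neither is named as primary. The covariate list for the Cox model is closed.

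Under Sample size calculation and power analysis, the calculation is made "with 2-sided testing and alpha set at 0.05, and following a Cox proportional hazards regression method".

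Under Recruitment, screening, and baseline visits, every candidate completes "an initial screening assessment which includes age, educational background, vision, hearing, diagnosis, heart function grade, etc". Randomization and blinding places allocation after baseline data collection, and stratifies by four wards and smoking status.

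For baseline data, Data analyses first plans descriptive summaries and then adds: "Differences in baseline characteristics between the control and intervention groups will be detected using ANOVA test", or a chi-square test for categorical variables.

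**The concern.** Settings and participants admits adults from 18 upwards, with AMI, ACS, or emergency or elective PCI. In so mixed a population, age, index diagnosis and heart function grade can reasonably be expected to predict MACEs. They are known before allocation, so a prespecified model can use them without risk to type I error. Leaving them out gives up some power in a trial sized at exactly 80%, with no margin.

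The plan does test baseline characteristics between the arms. Under randomisation any difference found is due to chance, so the tests answer no useful question. A p-value is also a poor guide to whether an imbalance matters for the outcome.

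**Working it through.** **1. The plan's own figure.** The inputs come from Sample size calculation and power analysis: "a total of 2256 participants (752 per group) would provide 80% power to detect a 40% relative reduction"; "the incidence of MACEs is 10% for the control group and 6% for the intervention group, hazard ratio is 0.6"; "we anticipated a maximum attrition rate of 20% among all enrolled patients"; two-sided alpha 0.05.

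- Schoenfeld events: (1.960 + 0.842)² / (0.25 × (ln 0.6)²) = 120.3.
- Mean event probability: (0.10 + 0.06)/2 = 0.08. Per group: 120.3 / 0.08 / 2 = 752.
- Attrition: 752 / (1 − 0.20) = 940 per group, and 3 × 940 = 2820.

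The stated figures reproduce exactly. The expected events per pairwise comparison are 752 × 0.16 = 120.3.

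**2. What a prognostic score adds.** The documents give no prognostic strength, so it is varied. The simulation has two arms of 752, exponential survival, censoring at 3 years and marginal risks held at 10% and 6%. A normal baseline score has standard deviation SD on the log-hazard scale. There are 3,000 replicates per case. Each data set is fitted by Cox regression with arm only, and with arm plus score.

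Gain in effective events = (mean z adjusted / mean z unadjusted)² − 1.

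| SD | c-statistic | HR, arm only | HR, adjusted | SE, arm only | SE, adjusted | Gain |
|---|---|---|---|---|---|---|
| 0 | 0.50 | 0.584 | 0.584 | 0.1896 | 0.1897 | 0% |
| 0.50 | 0.645 | 0.590 | 0.586 | 0.1897 | 0.1898 | 2.6% |
| 0.75 | 0.71 | 0.590 | 0.581 | 0.1897 | 0.1899 | 5.6% |
| 1.00 | 0.77 | 0.582 | 0.564 | 0.1899 | 0.1902 | 11.7% |
| 1.25 | 0.81 | 0.584 | 0.553 | 0.1899 | 0.1905 | 20.6% |

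The standard error does not fall. The gain comes from the conditional hazard ratio lying further from 1.

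**3. In power and patients.** With effective events E = 120.3 × (1 + gain), power = Φ(√E × |ln 0.6| / 2 − 1.96). The equivalent number per group is 752 / (1 + gain).

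| c-statistic | Power by formula (80.0% without score) | Equivalent n per group | Simulated power, arm only → adjusted |
|---|---|---|---|
| 0.645 | 81.0% | 733 | 80.8% → 81.7% |
| 0.71 | 82.1% | 712 | 80.1% → 82.6% |
| 0.77 | 84.2% | 673 | 82.1% → 87.3% |
| 0.81 | 86.8% | 624 | 81.7% → 88.2% |

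Monte Carlo error is about 0.7 points. Across both methods the gain is about 1 to 2.5 points for c of 0.65 to 0.71, and about 4 to 7 points for c of 0.77 to 0.81.

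A separate simulation with 8,000 runs per case and risks of 10% and 1 − 0.9^0.6 = 6.1% agrees. Power went from 78.5% to 79.5% (c about 0.63), from 78.9% to 81.4% (0.71) and from 79.6% to 83.7% (0.75). The gains in effective sample were 2%, 6% and 12%.

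**4. Baseline tests.** Table 1 has 29 assessment rows marked at T0. If each were tested at 0.05, the expected number of chance findings is 29 × 0.05 = 1.45. The probability of at least one is 1 − 0.95²⁹ = 77% if the tests were independent. They are not: weight, BMI and waist circumference move together, for example. Nor does the article say that exactly these rows will be tested. The expected count does not depend on independence, but the 77% does.

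**The case against.** The strongest reply is that adjusting for the stratification factors is a standard, valid choice, and that a longer list is a preference. Much of this stands. Type I error and the stated 80% power are intact, and the confidence interval already allows for chance imbalance.

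Several further objections also stand:

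- The gain is small unless the covariates are strong, and nothing in the documents shows how well they predict a composite as broad as this one, which includes stable angina and revascularisation.
- The simulated comparator contains no site or smoking term. The c-statistics should therefore be read as what the new covariates add beyond the strata. One of the four wards is an emergency ward and may already carry some acuity.
- The gain is not entirely free, because the adjusted hazard ratio is conditional on more covariates and changes in meaning.
- The article does not name Cox as primary. If the unadjusted chi-square test were primary, the added covariates would do nothing for it.

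A reader might infer that the baseline tests will drive a post hoc choice of covariates. The article does not support this: it fixes the covariate list, nowhere links the tests to it, and keeps those who analyse the data unaware of assignment. Nor do the tests themselves cost power; they are simply uninformative.

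What remains is that the article fixes a closed list which leaves out prognostic variables it already collects. That choice has not been left to a later document.

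**Conclusion.** The point holds as an efficiency improvement. At the planned size, adding age, index diagnosis and heart function grade would gain about 1 to 2.5 power points if they are weak to moderate predictors (c 0.65 to 0.71), and about 4 to 7 if they are strong (c 0.77 to 0.81). At c = 0.71 this is worth about 752 − 712 = 40 evaluable patients per group. The result rests on the assumed prognostic strength, on proportional hazards, and on the plan's 10% and 6% event rates.

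It would be wrong to conclude that the planned analysis is biased or that the trial is underpowered as designed: the sample size reproduces exactly on its own inputs.

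One mismatch should be settled at the same time. Randomisation is stratified by four wards, but the model adjusts for study sites, and there are two hospitals.

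**What to change.** In Data analyses:

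- Name the adjusted Cox model as the primary analysis and the unadjusted chi-square test as supportive.
- Prespecify its terms: group; the actual randomisation strata (4 wards and smoking status); age as a continuous variable; index diagnosis; heart function grade, on a named scale.
- Give index diagnosis mutually exclusive levels with a stated hierarchy, because the entry categories overlap (a patient with AMI may also have PCI). Include a level for other CHD.
- State that the hazard ratio is conditional on these covariates.
- Keep the strata-only model as a sensitivity analysis.
- Report baseline characteristics descriptively by arm, and delete the ANOVA and chi-square tests.

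Cost: wording only, and no new data. Study status and recruitment says that analysis had not started when the article was submitted. The model gains one parameter for age, three for a four-level diagnosis factor and at least one for heart function grade, so five or slightly more. Four wards in place of two sites add two. Against about 120 events per pairwise comparison this is affordable. The other cost is that the main hazard ratio is conditional on more than the strata.
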